##### Assessments

All women enrolled in the study will complete a baseline survey following informed consent and a follow-up survey immediately after their clinical visit. Surveys will be administered on tablets in a private room within the clinic and will use REDCap for data collection. Each survey will take approximately 25 minutes to complete, and women will receive US $25. Survey measures are described later and in Table 2.

A subsample of 20 intervention (*i.ARTs*) arm women and 10 providers will be randomly chosen to participate in an exit interview. This interview will occur either at the baseline visit or up to 1 month after *i.ARTs* use at the participant’s convenience. We will select every fourth woman in the intervention arm to complete the exit interview. Providers will be selected based on the number of *i.ARTs* participants they served in the first year of the pilot (we will randomly select 10 providers from all providers who serve above the median number of *i.ARTs* clients, which ensures that providers will have sufficient experience with the tool to provide feedback) and exit interviews with providers will be conducted in the final 3 months of data collection. These interviews will focus on patient and provider experiences with *i.ARTs* acceptability, feasibility, and usability, and the most useful ways to improve its integration into clinical practice. This will also include discussions of how women shared the results from the patient decision aid with their provider. Exit interviews will take approximately 30 minutes and participants will be provided US $30 in compensation.

The study will also use all 180 participants’ electronic medical records (EMRs) to assess the impact of the intervention on clinical outcomes (Table 2). The informed consent process will include the EMR abstraction release form and detailed information about the data abstraction process. Study staff will abstract data on viral suppression (all women), ART modality, clinic attendance (all women), and medication refill data (women on oral ART) from EMRs into a REDCap database. Abstraction will include data from 1-year prebaseline to 6 months postbaseline. This timeline is based on the frequency of HIV clinic visits (ie, approximately every 3 months) to ensure that women have at least one visit in the follow-up period.

**Table 2 table2:** *i.ARTs*^a^ pilot study measures in phase 3.

Outcomes			Description of measures

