**Primary**			Assessed after *i.ARTs* use among women using i.ARTs (n=90)
	Feasibility	Adaptation of Thabane et al’s [59] framework [60,61] for assessing pilot studies: Process, Resources, Management, Science	
	Acceptability and usability	Acceptability [62] and CSQ-8^b^ [63] to measure satisfaction with *i.ARTs*; exit interviews about *i.ARTs* features/protocol [62]	
**Secondary**			Assessed in baseline survey and postvisit survey for all women (n=180)
	Decisional conflict	Decisional Conflict Scale (16 items) [52]; satisfaction with the chosen method [64]	
**Tertiary**			Assessed 1-year prebaseline, at baseline, 3 months, and 6 months (all women; n=180)
	Viral suppression	Viral suppression, defined as viral load below limit of detection per assay used	
	Medication refills	Missed doses; report of medication refills/pharmacy pick up (WWH^c^ on oral ART^d^)	
	Clinic attendance	Missed or cancelled medical visits (<2 visits in a 6-month period for oral ART; missed monthly visit for LAI^e^ ART)	
	ART modality	Adoption of LAI among patients who are virally suppressed	
**Moderators**			Assessed at baseline
	Sociodemographics	Race/ethnicity, age, housing stability, education, employment, income, distance from clinic, relationship status, children	
	Depression/anxiety	PHQ-8^f^ (depression) [65]; GAD-7^g^ [66]	
	Substance use	ASSIST^h^ [67], an 8-item measure of problematic substance use	
	Stigma/discrimination	MDS^i^ to measure racial discrimination [68]; HIV-related stigma	
	Self-efficacy	HIV-ASES^j^ [38]	
	ART-related knowledge	Adaptation of Feldman’s [69] scale of oral ART knowledge; BMQ^k^ [70]	

^a^*i.ARTs*: i.ART+support.

^b^CSQ-8: 8-item Client Satisfaction Questionnaire.

^c^WWH: women with HIV.

^d^ART: antiretroviral therapy.

^e^LAI: long-acting injectable.

^f^PHQ-8: 8-item Patient Health Questionnaire.

^g^GAD-7: 7-item General Anxiety Disorder scale.

^h^ASSIST: Alcohol, Smoking and Substance Involvement Screening Test.

^i^MDS: 10-item Multiple Discrimination Scale.

^j^HIV-ASES: HIV Treatment Adherence Self-Efficacy Scale.

^k^BMQ-18: 18-item Beliefs and Medicines Questionnaire.

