#### Analysis

The primary outcomes of feasibility, acceptability, and usability will be assessed descriptively. We will compare ART-related decisional conflict, clinic attendance, viral suppression, and medication refills between and within the 90 women in each arm (baseline vs postvisit surveys and EMR data at 3 and 6 months). For normally distributed data, we will first use *t* tests to compare the 2 arms and then use regression methods to develop a multivariable model of the outcome, with arm membership as the principal covariate, while controlling for the moderators listed in the previous sections and in Table 2. For nonnormally distributed data, we will employ chi-square tests and logistic regression; distributional properties of the outcome will determine the type of logistic regression (eg, binary, multinomial, or ordinal logistic regression models). We note that these are examples and the final approach will be determined based on the distribution of the data.

The primary analysis will use an intent-to-treat approach with the use of *i.ARTs* as a 1-time exposure, with α=.05, and 2-sided tests. The number of moderators included in the regression model will be used to make a Bonferroni adjustment to the α value. A secondary efficacy analysis will explore actual treatment taken. Our exploratory tertiary outcomes of viral suppression, clinic attendance, chosen ART modality, and medication refills will compare both between and within *i.ARTs* and control arm women (ie, baseline and postvisit surveys and EMR data at 3 and 6 months); we will also examine these outcomes for women who do not change regimens. We will use prebaseline EMR data to control for previous viral load. We will also compare how many women in each arm change modalities postbaseline to assess *i.ARTs’* accuracy in identifying which HIV treatment modality is the best match. Sensitivity analyses will determine whether assumptions associated with each model are defensible.

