### Expected Challenges

As this study is set in real-world clinical settings, we expect challenges to incorporating *i.ARTs* delivery into existing clinical workflows. These include considerations such as available space for participants to complete *i.ARTs*, tech support for the computerized tool and printout, staffing resources, and limited clinician time with each patient to discuss the decision aid results. The study team will work with the clinic staff to determine how to ensure efficient delivery of *i.ARTs* in the clinical setting. Exit interviews will be used to collect data on these challenges to inform further scale-up or dissemination efforts of *i.ARTs* outside of the Miami-based clinic*.*

As LAI ART is being administered in a real-world setting, participating clinicians are subject to existing, and possibly changing, FDA approvals. While phase 3 trials are currently testing LAI ART for nonadherent patients, *the FDA-approved LAI ART formulation is only for virally suppressed patients*. To ensure *i.ARTs* incorporates all relevant drivers of ART use for all women, we aim to include nonadherent women in aim 3, pending FDA approval. If FDA approval only exists for virally suppressed WWH when aim 3 starts, then we will limit the pilot test to that population. Should FDA approval for nonadherent patients begin in the middle of the pilot, we may adjust eligibility criteria to ensure a standard participant population throughout the pilot period. The study team will carefully monitor developments in ART treatment technologies and adapt accordingly. In addition, LAI ART was initially approved as a monthly injection, and the US FDA has approved a bimonthly (ie, every 8 weeks) formulation of LAI ART. This may also affect women’s preferences as the study is rolled out.

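### Of the year of prebaseline EMR data, only previous viral load is named as a covariate, so the exploratory attendance and refill models leave out their own baseline value

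*Protocol article*

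**What the plan says.** The Assessments section sets the EMR window: "Abstraction will include data from 1-year prebaseline to 6 months postbaseline". The variables include "clinic attendance (all women), and medication refill data (women on oral ART) from EMRs into a REDCap database", together with viral suppression and ART modality. Table 2 gives the time points of all tertiary outcomes as "Assessed 1-year prebaseline, at baseline, 3 months, and 6 months (all women; n=180".

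The Analysis section makes attendance and refills comparative outcomes: "We will compare ART-related decisional conflict, clinic attendance, viral suppression, and medication refills between and within the 90 women in each arm". It specifies a multivariable model "with arm membership as the principal covariate, while controlling for the moderators listed in the previous sections and in Table 2". The Table 2 moderators are sociodemographics (including housing stability and distance from clinic), depression and anxiety, substance use, stigma and discrimination, self-efficacy and ART-related knowledge. Past attendance and past refills are not among them. For the EMR history the section then says: "We will use prebaseline EMR data to control for previous viral load". No other covariate use of that history is stated.

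Expected Challenges adds a condition on the population: "If FDA approval only exists for virally suppressed WWH when aim 3 starts, then we will limit the pilot test to that population".

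**The concern.** A woman's own record of attending or refilling is a natural predictor of the same behaviour over the next 6 months. The plan accepts the principle of adjusting for EMR history but applies it to one of the outcomes. The attendance and refill models would then carry the history of a different outcome and not their own.

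Previous viral load may also be a weak substitute. If the pilot is restricted to virally suppressed women, it may vary little, while attendance and refill histories can still differ between women.

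At stake is the precision of preliminary estimates from 180 women, and how far a difference in past attenders or refillers between the arms can move those estimates. The stated primary and secondary outcomes are not affected.

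**Working it through.** **The plan's own power figure.** Power Analysis and Sample Size gives means of 21 (SD 16) and 28 (SD 18), 90 per arm, two-sided alpha .05 and 80% power, for decisional conflict. Pooled SD = √((16² + 18²)/2) = 17.03, so d = 7/17.03 = 0.411. Power is 78.7% by the normal approximation and 78.3% by the t test, so the figure is reproduced to within 2 points. It does not depend on the EMR covariates. For the tertiary outcomes the article gives only a 35% non-adherence rate and no target difference.

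**Assumptions.** The article gives no correlation between prior and follow-up attendance or refills, so a range is shown. The comparison rates of 20% and 17% against 35% are also assumptions. All gains below are measured against a model with no covariates.

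**Continuous outcome.** Adjusting for a baseline value with correlation r multiplies the residual variance by (1 − r²). The detectable difference at 80% power is (1.960 + 0.842) × √(2/90) × √(1 − r²) SD, and the effective total N is 180/(1 − r²).

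| r | Variance removed | Detectable difference (SD) | Effective N |
|---|---|---|---|
| 0 | 0% | 0.418 | 180 |
| 0.3 | 9% | 0.398 | 198 |
| 0.5 | 25% | 0.362 | 240 |
| 0.7 | 49% | 0.298 | 353 |

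**Binary outcome, linear risk-difference scale.** For 35% vs 20%, SE = √((0.35×0.65 + 0.20×0.80)/90) = 0.0656. Then 0.15/0.0656 − 1.96 = 0.326, which is 63% power. Scaling the variance by (1 − r²) gives 67% at r = 0.3, 70% at 0.4 and 75% at 0.5.

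**Binary outcome, logistic model.** This is the model family the article names for such data. The simulation used 35% vs 17%, 90 per arm, 1,500 runs per setting, and a dichotomised prior value added to the model.

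| Latent correlation | Power without prior value | Power with prior value | Gain (points) |
|---|---|---|---|
| 0.3 | 80.1% | 81.7% | 1.6 |
| 0.5 | 76.4% | 80.1% | 3.7 |
| 0.7 | 78.6% | 87.1% | 8.5 |

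The scatter in the unadjusted column is simulation error: √(0.79×0.21/1500) is about 1 point. These gains are smaller than the linear ones at the same nominal correlation because dichotomising a latent variable weakens its correlation with the outcome.

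**Validity.** With no true difference, the unadjusted logistic test rejected in 4% to 5% of runs at every correlation.

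**Chance imbalance.** If 35% of women had poor prior attendance (an assumption), the SD of the between-arm difference in that proportion is √(2×0.35×0.65/90) = 7.1 points, with a 95% range of about ±14. Only part of this reaches the outcome. On the linear scale with equal prevalence before and after, a 7.1-point imbalance moves the estimated arm difference by r × 7.1, which is 2.1 points at r = 0.3 and 3.6 at r = 0.5.

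**The case against.** A reader might infer that the EMR models adjust for previous viral load and nothing else. The Analysis section does not support that, because the Table 2 moderators are in the models too. Several of them, such as distance from clinic, housing stability and adherence self-efficacy, plausibly predict attendance and refills. The relevant correlation is therefore the partial one, given the moderators and previous viral load, and the gains above are upper limits. This objection stands in full.

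A reader might also infer bias or false-positive findings. Randomisation rules that out: the unadjusted test keeps its level, and its standard error already allows for chance imbalance. What is lost is precision, and protection in the particular sample drawn.

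It can further be said that a condensed article leaves covariate lists to an analysis plan, and that the article keeps its final approach open. This stands only in part. The article does state a covariate set, and the caveat about the final approach concerns the choice of test and model by the distribution of the data. The planned within-arm comparisons use earlier values, but they do not give a baseline-adjusted comparison between arms.

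The inputs also flatter the result. The 35% is general non-adherence, not an attendance or refill rate. Refills exist only for women on oral ART, so that comparison will have fewer than 90 per arm if any women are on LAI ART. The article also plans a Bonferroni reduction of alpha, whereas .05 is used here. Previous viral load over a 1-year window could still vary among women who are suppressed at entry, so its weakness as a substitute is possible rather than certain.

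Lastly, Table 2 defines attendance differently for oral and LAI ART. Prior attendance is then not the identical measure for women who switch, but it can still serve as a covariate.

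**Conclusion.** The point holds as a minor one. Of the abstracted EMR history only previous viral load is named as a covariate, and the between-arm models for attendance and refills omit a baseline value that the study will already have.

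The benefit of including it is real but modest: a variance reduction of at most about 9% to 25% for correlations of 0.3 to 0.5, and roughly 2 to 8.5 points of power in a logistic model at latent correlations of 0.3 to 0.7. Both are measured against a covariate-free model and rest on assumed correlations and event rates. The gain over the plan's own model cannot be computed from the article.

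The article labels these outcomes exploratory ("Our exploratory tertiary outcomes of viral suppression, clinic attendance, chosen ART modality, and medication refills will compare both between and within"), so no confirmatory conclusion is at risk.

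**What to change.** Replace the sentence on previous viral load with wording such as: *Each EMR outcome's between-arm model will include that outcome's own prebaseline value: prior-year visit attendance for clinic attendance, prior-year refill record for medication refills (women on oral ART), and previous viral load for viral suppression.*

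The cost is one sentence. No new data, visits or participants are needed. A rule set in advance is required for women with less than a year of records at the clinic. The refill adjustment does not deal with women who leave that outcome by moving to LAI ART; that is a separate matter. Giving these terms priority over the moderators, or reporting a standardised risk difference, is optional.

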While preliminary research suggests that most WWH would prefer LAI ART over their current daily oral medication [18], this research has also identified multilevel barriers to LAI ART uptake. At the *individual level*, these include women’s concerns about side effects, pregnancy-related interactions, and drug resistance if LAI ART is discontinued without oral ART initiation; at the *clinic level*, barriers include medical mistrust due to historic sterilization campaigns [19] and lack of provider knowledge and willingness to offer LAI ART; and at the *structural level*, barriers include gender-specific socioeconomic inequalities and dynamics such as low-wage employment with unstable scheduling, lack of transportation, and care-taking responsibilities. Furthermore, FDA indication still requires viral suppression via oral ART prior to initiating LAI. These multilevel barriers could all complicate the frequent visits that LAI ART administration will require [18,20-23]. WWH and providers may benefit from tools and strategies that help them to identify and address barriers that prevent uptake of, and adherence to, LAI ART.

Shared decision making in medical settings is often accomplished using patient decision aids. These evidence-based tools promote equity in medicine by increasing patients’ knowledge, decision-making power [24,25], and health outcomes [26-28]. This approach can also lower medical paternalism [24,29-31]. Patient decision aids can improve medication adherence directly [32], as well as through mediating factors (eg, patient satisfaction [33-35], efficacy [36-38], and communication) [33,39,40]. These tools are ideal for preference-sensitive decisions with multiple options [41,42]; however, no patient decision aids yet exist to facilitate women’s choice between HIV treatment modalities. New tools are urgently needed to ensure the successful and equitable integration of new technologies such as LAI ART into clinical settings [43].

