#### Study Procedures

##### Randomization

Following informed consent and the baseline assessment (discussed later), we will use a web-based system to randomize women (1:1) to the *i.ARTs* intervention arm (n=90) or to the standard-of-care control arm (n=90). Neither participants nor researchers will be blind to study condition. Women in the control arm will receive standard of care as it exists at the time of LAI ART roll out: providers will offer women information about LAI ART and may strongly suggest which option she should choose. Women who participated in the focus groups will not be eligible for inclusion.

Women in the intervention arm will use *i.ARTs* as part of their regular participant visit. While the complete content of *i.ARTs* will be finalized in phase 2, the web-based *i.ARTs* app will guide WWH through the following activities: (1) provide education on different ART modalities, (2) utilize value clarification methods to guide women in ranking the prominence of relevant barriers and facilitators that may impact adherence to various ART modalities, (3) collect information on participant health history, (4) generate a suggested ART modality based on previous steps, (5) assist WWH in developing questions for their health care providers, and (6) generate an individual profile description as well as individualized suggestions to support adherence based on the modality selected (eg, a woman may be profiled as having transportation challenges; *i.ARTs* would suggest solutions—arranged transportation or transportation vouchers—that the clinic could employ to address these challenges). Participants will take a printout of this profile to their clinic visit with their provider. Intervention arm participants will receive US $15 for *i.ARTs* use.

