#### Power Analysis and Sample Size

Our sample size is based on our secondary outcome of decisional conflict, as our primary outcomes of acceptability and feasibility are only assessed in the intervention group (as the control group will not experience *i.ARTs*). Scale developers use a moderate effect size (0.3-0.4) to determine sample size. Using the average weighted means and SDs from prior studies [52], we calculated sample size for α=.05, power=0.8 for an independent samples *t* test. Assuming a mean score of 21 (SD 16) in the intervention (*i.ARTs*) group and a mean score of 28 (SD 18) in the control group, the sample size of 90 in each group, for a total of 180, provides 80% power. Our tertiary outcomes are exploratory, but as 35% of US women are not adherent after 6 months, we are powered to detect basic differences between the intervention and control arms.

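### Comparing post-baseline modality changes by arm cannot show how accurate the i.ARTs suggestion is, and the count as worded mixes LAI starts with later switches

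*Protocol article*

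**What the plan says.** The Analysis section names both a measure and the conclusion to be drawn from it. The measure reads: "We will also compare how many women in each arm change modalities postbaseline to assess". The conclusion it is meant to support concerns the tool's "accuracy in identifying which HIV treatment modality is the best match". The section does not define what counts as a change, from which moment changes are counted, or which direction is favourable.

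Four other places bear on this:

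- Randomization: the baseline assessment comes before randomization, and so before any use of i.ARTs. Among its functions, the app will "generate a suggested ART modality based on previous steps".
- Randomization, control arm: "providers will offer women information about LAI ART and may strongly suggest which option she should choose". Power Analysis and Sample Size confirms that controls have no exposure to the tool: "as the control group will not experience" i.ARTs.
- Table 2, tertiary outcomes, ART modality: "Adoption of LAI among patients who are virally suppressed".
- Introduction: "FDA indication still requires viral suppression via oral ART prior to initiating LAI".

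**The concern.** Two different events can be recorded as a modality change after baseline. A woman on oral ART may discuss the options at the index visit and start LAI. That is a change, and it may be exactly what a well-working aid should produce. Another woman may start on her chosen modality and later leave it. That is also a change, but it may point to a poor match. The planned count adds the two together.

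There is a second problem, which does not depend on how change is defined. Accuracy is a property of a suggestion judged against something. Only the i.ARTs arm has a suggestion from the tool, and the article plans no analysis that compares it with what the woman chose or with what she was taking at 6 months.

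At stake is the conclusion on match. Matching women to a modality is the tool's stated purpose, yet a higher count in the i.ARTs arm could be reported as either good or poor accuracy, with nothing in the plan to decide between them.

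**Working it through.** The documents give no rate, effect size or power for modality change, so there is no figure of the plan's own to reproduce. The check has two parts.

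**1. Does the measure support the stated conclusion?**

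- A suggestion exists in the i.ARTs arm only (Randomization; Power Analysis and Sample Size).
- The suggestion is not among the items listed for record abstraction (Assessments: viral suppression, modality, attendance, refills), and no analysis uses it.
- The count can therefore be computed in both arms without knowing what i.ARTs suggested to anyone. A quantity that takes the same value whatever the tool suggested cannot measure the accuracy of the suggestion.

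**2. What does the count respond to?**

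Assume that all women are on oral ART at baseline. The Introduction makes this the usual route to LAI, but the eligibility criteria do not require it. All rates below are assumptions. Let

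- u = proportion starting LAI at or soon after the index visit,
- r = proportion of those starters who later return to oral ART,
- o = proportion of women who first stay on oral ART and later start LAI.

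Per 90 women:

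- ever changed since the baseline assessment = 90 × [u + (1 − u) × o]
- later switch away from the modality chosen at the visit = 90 × [u × r + (1 − u) × o]

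The return rate r does not appear in the first formula: a woman who starts LAI is already a changer, whether or not she stays on it.

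| Scenario (i.ARTs vs control) | Ever changed | Later switch |
|---|---|---|
| 0. u 0.40 vs 0.20; r = o = 0 in both | 90×0.40 = 36 vs 90×0.20 = 18 | 0 vs 0 |
| A. u 0.50 vs 0.30; r 0 vs 0.20; o 0 vs 0.10 | 90×0.50 = 45.0 vs 90×(0.30+0.07) = 33.3 | 0 vs 90×(0.06+0.07) = 11.7 |
| B. u 0.50 vs 0.30; r 0.10 and o 0.05 in both | 90×(0.50+0.025) = 47.25 vs 90×(0.30+0.035) = 30.15 | 90×(0.05+0.025) = 6.75 vs 90×(0.03+0.035) = 5.85 |
| C. u 0.40 in both; r 0.05 vs 0.15; o 0.05 vs 0.10 | 90×(0.40+0.03) = 38.7 vs 90×(0.40+0.06) = 41.4 | 90×(0.02+0.03) = 4.5 vs 90×(0.06+0.06) = 10.8 |

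- In A, the arm in which nobody leaves her chosen modality has the higher count.
- In B, staying with a given modality is equally likely in both arms, and the difference in the count is almost all uptake.
- In C, uptake is equal and later switching differs by 6.3 women per 90 (10.8 − 4.5), but the count differs by only 2.7 (41.4 − 38.7).

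If change were instead scored as baseline modality versus 6-month modality, a woman who starts LAI and reverts would count as unchanged, and a possible mismatch would drop out.

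**The case against.** The best defence concerns the word postbaseline. Randomization places the baseline assessment before i.ARTs use. Assessments, however, allows the exit interview about the tool to take place at the baseline visit, so there the term covers the whole index encounter. The Analysis section also lists chosen modality as an outcome of its own before turning to changes, which would be redundant if changes simply meant uptake. Table 2's adoption outcome is narrower too, being limited to virally suppressed women. The authors may well have meant later switches. As control providers may steer the choice, comparing later switching by arm is then a reasonable indirect signal of how well choices made with and without the aid hold up.

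This stands in part. A reader might infer that the planned measure counts uptake instead of match. The documents do not support so firm a statement, because the later-switch reading is open and the overlap with Table 2 depends on which reading is taken. A reader might also infer from 36 versus 18 that a well-matching tool will look twice as bad as usual care. Those rates are assumed, and the article never says that change is to be read as inaccuracy.

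It may also be said that an exploratory counting rule can wait for a fuller document. That answers the missing definition. It does not answer the inference, which the article itself states. On the most favourable reading, comparing arms shows persistence with a choice, and the tool's suggestion still does not enter it.

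**Conclusion.** The point holds in a limited form. On any reading, the planned comparison cannot establish the accuracy of the i.ARTs suggestion, because controls have no suggestion and the suggestion in the i.ARTs arm is not compared with anything. This rests on the text alone. As worded, the count also fails to separate LAI starts from later switches and has no stated direction. The size of that ambiguity is unknown: the scenarios show only that the count can rank the arms either way, under assumed rates and with all women on oral ART at baseline. The consequence is confined to one exploratory claim. The primary outcomes are descriptive and the sample size rests on decisional conflict, so neither changes. It should be corrected before phase 3 begins, because a suggestion that is not stored prospectively may not be recoverable.

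**What to change.** Replace the sentence in Analysis with three separate reports.

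1. In the i.ARTs arm only, store the suggested modality for each woman and report concordance of suggested, chosen and 6-month modality with 95% confidence intervals. With all 90 women contributing, the half-width is at most about 1.96 × √(0.5 × 0.5 / 90) = 0.103, or 10 percentage points. Describe the result as whether the suggestion was followed and kept.
2. Report LAI uptake by arm, separately from any later change.
3. Define later switching as a change away from the modality chosen at the index visit. Report it by arm, overall and by chosen modality, and call it persistence, not accuracy.

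The cost is modest: retaining an output the app is planned to generate, recording the modality chosen at the visit, deriving one variable from the records, and rewording. There are two drawbacks. Report 1 has no control comparison. Report 3 depends on the oral/LAI mix, which is chosen after randomization. In scenario B, return and late-start rates are identical in the two arms, yet later switches are 6.75 versus 5.85 per 90 because the mix differs. Splitting by chosen modality shows this, but those subgroups are no longer randomized, so report 3 should be presented as descriptive.
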